### Trial design {8}

The present trial is a prospective, randomized, open-label trial to prove the non-inferiority of TAVR-CMR compared to TAVR-CT to guide TAVR. The final analysis will include 226 consecutive patients scheduled for TAVR. According to previous studies, approximately 45% of the patients are female [9]. Therefore, to guarantee gender equity, we aim to enroll at least 80 female patients. Patients will be randomized in a 1:1 fashion to receive a predefined TAVR-CMR protocol or to receive a standard contrast-enhanced TAVR-CT protocol within 2 weeks after inclusion. Inclusion and exclusion criteria are presented below. A detailed study flowchart is presented by Fig. 1. Follow-up for the primary objective will be performed before discharge after TAVR. Extended analysis and clinical follow-up is planned after 2 years.

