#### Strategies to improve adherence to interventions {11c} and relevant concomitant care permitted or prohibited during the trial {11d}, adverse event reporting and harms {22}

Cross-over between allocated groups because of clinical reasons should be minimized and will be documented. Non-contrast CT scans to assess calcium load if CMR is not sufficient should also be minimized especially by discussing special cases within the TAVR team including TAVR operators and radiologists. Patients included in the study are informed that they should not participate in another experimental study during the study period. Furthermore, no restrictions are made regarding clinical care of the patients. Adverse events will be immediately reported to the sponsor.

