### Sample size {14} and recruitment {15}

Sample size estimation for the primary endpoint is based on previous data indicating a rate of 4% of early deaths, 4% of valve regurgitation > mild, and 0.4% of reinterventions after TAVR [10]. Therefore, we estimate an implantation success rate of 92% in both study groups. For a non-inferiority margin of 9%, hence 113 patients per group should be included to achieve a statistical power of 80%. A drop-out rate of 10% is assumed. Therefore, it is planned to include a total of 250 patients in the trial.

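### The final analysis is fixed at the post-drop-out number (226) instead of all 250 randomised, which with discretionary withdrawal leaves room for outcome-related exclusion

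*Protocol article*

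**What the plan says.** Four parts of the protocol article bear on who is analysed.

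- **Trial design {8}**: "Patients will be randomized in a 1:1 fashion", and "The final analysis will include 226 consecutive patients scheduled for TAVR". The primary outcome is read before discharge after TAVR.
- **Sample size {14}**: 113 per group for a 9-point margin and 80% power, with 92% success expected in both arms. Then "A drop-out rate of 10% is assumed. Therefore, it is planned to include a total of 250 patients in the trial".
- **Eligibility {10} and Criteria for discontinuing {11b}**: the same withdrawal list appears in both. It includes significant protocol deviation, noncompliance, adverse event and an administrative decision by the investigator. It also includes patient request, pregnancy, other safety concerns and loss to follow-up. It applies to both arms.
- **Strategies to improve adherence {11c}**: "Cross-over between allocated groups because of clinical reasons should be minimized and will be documented". No analysis rule is attached.

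The section headed with item {20c} (non-adherence and missing data) describes contacting patients, recording the date and reason of withdrawal, and documenting outcomes where possible. It does not say how withdrawn or crossed-over patients are analysed. Under Blinding {17a}, allocation, image reading and TAVR operators are open-label; endpoint evaluators are blinded.

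**The concern.** A sample-size section ordinarily gives an evaluable target and inflates it for drop-out. Here the design section takes the target and states it as the population of the final analysis, about 24 fewer than the number randomised. An analysis plan that used all randomised patients would contradict that sentence.

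Two features make this more than loose wording. First, the endpoint is read in hospital at a single centre, so ordinary loss to follow-up hardly explains 10%. Second, several withdrawal reasons are discretionary, arise after randomisation, and can be applied by staff who know the arm and the scan result. Blinded endpoint evaluation does not control who leaves the dataset. The protocol itself foresees insufficient CMR scans and cross-over for clinical reasons.

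In a non-inferiority trial, selective loss of failures from the new strategy moves its success rate towards the comparator's and can produce a false claim.

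**Working it through.** **Inputs.** From Sample size {14}: success 92% in both arms, margin 9 points, power 80%, drop-out 10%, enrolment 250. From Trial design {8}: 226 analysed, 1:1 allocation, hence 125 randomised per arm. The sample-size section states no alpha.

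**1. Reproduce the plan's figures.**

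n per arm = (z₁₋α + z₀.₈₀)² × 2 × 0.92 × 0.08 / 0.09²

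At one-sided 0.05: (1.645 + 0.842)² × 0.1472 / 0.0081 = 112.4, so 113 per arm and 226 in total. This matches. (At one-sided 0.025 the result is 143 per arm, which does not match. That is a separate matter.)

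Drop-out: 226 / 0.90 = 252 and 226 × 1.10 = 249. The stated 250 agrees with both to rounding. The gap is 250 − 226 = 24, or 9.6%, about 12 per arm. So 226 is the evaluable target.

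**2. If drop-out is unrelated to outcome.**

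Power = Φ(0.09 / SE − 1.645), with SE = √(2 × 0.92 × 0.08 / n).

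- n = 125: SE = 0.0343, power 83.6%.
- n = 113: SE = 0.0361, power 80.2%.

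There is no bias, only a loss of 3.4 points of power.

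**3. If drop-out is related to outcome.** This is an illustration; its assumptions are not in the documents. True CMR success is 83% (exactly at the margin) and CT success 92%. 125 CMR patients are randomised, x CMR failures are dropped, and 113 CT patients are analysed after random loss.

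CMR success analysed: p = 0.83 × 125 / (125 − x)

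False non-inferiority rate: Φ[(0.09 − (0.92 − p)) / SE − z₁₋α], with SE² = 0.92 × 0.08 / 113 + p(1 − p) / (125 − x)

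For x = 2: p = 103.75 / 123 = 0.8435; SE = 0.0415; (0.09 − 0.0765) / 0.0415 − 1.645 = −1.32; Φ = 9.3%.

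| CMR failures dropped | CMR success analysed | Difference from CT (points) | False claim, one-sided 0.05 | False claim, one-sided 0.025 |
|---|---|---|---|---|
| 0 | 83.0% | −9.0 | 5.0% | 2.5% |
| 2 | 84.3% | −7.7 | 9.3% | 5.1% |
| 4 | 85.7% | −6.3 | 16.6% | 9.9% |
| 6 | 87.2% | −4.8 | 27.6% | 18.1% |
| 12 | 91.8% | −0.2 | 78.4% | 68.1% |

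The approximation is adequate. A simulation that dropped each CMR failure with probability 10% or 20% (on average 2.1 or 4.2 dropped) gave 10.3% and 18.4% at one-sided 0.05.

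**4. Direction.** Removing 2 CT failures and no CMR failures gives CT success of 115 / 123 = 93.5%. The difference becomes 83.0 − 93.5 = −10.5 points, against non-inferiority. Removing 2 failures from each arm gives 84.3 − 93.5, about −9.1 points, almost unchanged. The bias towards non-inferiority therefore needs an imbalance between arms.

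**The case against.** A reader might infer that the plan discards the patients withdrawn for deviation, noncompliance or adverse event, and that these are CMR planning failures. The documents do not support that. Nothing says that withdrawn patients leave the analysis, or that the roughly 24 are those withdrawn for these reasons. The figure 226 may simply be the sample-size target carried into the design section. The withdrawal list is broader than those reasons, covers both arms, and sits under discontinuation of the intervention, not under analysis sets. The protocol also intends to document outcomes where possible and to record cross-overs.

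Nor is the direction fixed. A CMR patient who crosses to CT may still have a successful implantation, so dropping that patient would not raise the CMR rate. Kidney injury from iodinated planning contrast would mainly concern the CT arm, and it belongs to the secondary safety endpoint. The extreme calculation, 104/113 = 92.0% against 104/125 = 83.2%, an 8.8-point shift, requires all 12 CMR drop-outs to be failures with no counterpart under CT. It is a bound, not an estimate.

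Finally, analysis sets are commonly defined in an analysis plan, which is not shown, so their absence is no fault. All of this stands and limits the claim. It does not remove the sentence that fixes the final analysis at 226 when 250 are randomised.

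**Conclusion.** The point holds as a defect in what the protocol states. The analysed number is the post-drop-out target, and beside it stand discretionary withdrawal criteria in an open-label trial. Followed as written, this permits a reduced population open to outcome-related exclusion. It is not evidence that such exclusion is planned.

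The consequence depends on why patients leave. With drop-out unrelated to outcome, the cost is 3.4 points of power. With 2 to 4 failures lost selectively from the CMR arm, the false-claim rate is about 9% to 17% instead of 5%, given true success of 83% and 92% and a one-sided 0.05 test. At one-sided 0.025 it is about 5% to 10% instead of 2.5%.

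**What to change.** 1. In Trial design {8}, say that 226 is the evaluable target used for sample size, and that the primary analysis includes all randomised patients by allocated arm.
2. In {10} and {11b}, separate stopping or changing the allocated imaging from withdrawal from follow-up. Patients with a protocol deviation or noncompliance stay in the trial, and their discharge outcome is recorded unless consent is withdrawn.
3. Report a per-protocol analysis in support, with cross-overs listed by arm, because an as-randomised analysis can itself draw the arms together when patients cross over.

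How a patient who never reaches TAVR counts towards the endpoint is a choice for the sponsor, and this point does not prescribe it.

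The cost is protocol wording, retrieval of some in-hospital outcomes, one extra analysis and possibly a slightly lower observed success rate. Under the plan's own assumption of 92% in both arms, power rises from 80.2% to 83.6% at one-sided 0.05 if all 250 are analysed.

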**Fig. 1 Fig1:**
[figure not shown]
Study design flow chart. *TAVR*, transcatheter aortic valve replacement; *CMR*, *cardiovascular magnetic resonance*; *CT*, *computed tomography*

### Patient involvement

Our present study included no involvement of public or patient representatives concerning the design of the protocol.

## Methods

### Study setting {9}

This project will be carried out as a single-center study located at the University Clinic for Internal Medicine III (Cardiology) and the University Clinic of Radiology at Innsbruck Medical University (Radiology Core Lab). Moreover, the infrastructure available at Innsbruck Medical University including the Department of Medical Statistics, Informatics and Health Economics as well as the Clinical Trial Center will assist the conduct of the study and warranting the successful accomplishment of the project.

### Eligibility criteria {10}

Patients aged from 19 to 99 years with a decision for TAVR for symptomatic severe aortic stenosis according to the decision of the local “heart valve team”. Screening will be performed during the “heart valve team” meetings, which are conducted once a week. Eligible patients will then be asked for study participation and checked for the following inclusion and exclusion criteria.

Inclusion criteria:Signed informed consentSevere aortic stenosis according to recent guidelines (aortic valve area ≤ 1.0cm^2^ or aortic valve index ≤ 0.6 cm^2^/m^2^) [1]Typical symptoms of severe aortic stenosis like shortness of breath, angina, or syncopeDecision for TAVR according to the local “heart valve team” including cardiologists and cardiac surgeons

Exclusion criteria:Contraindications to perform CMRContraindications to perform CTContraindications for TAVR or reduced life expectancy < 1 year.Known hypersensitivity to CMR or CT contrast agentsKillip class ≥ 3Childbearing potential or inability to exclude pregnancyInability to understand and follow study-related instructionsSevere renal insufficiency requiring renal replacement therapySevere hepatic insufficiency (Child–Pugh class B or C)Post organ transplantationParticipation in another clinical study

Withdrawal criteria:Patients request without giving reasonsAdministrative decision by the investigatorPregnancySignificant protocol deviationSubject noncomplianceAdverse eventOther safety concern of the investigator or sponsorLost to follow-up

### Who will take informed consent? {26a}

After the identification of the individual patient, he will be asked by a senior physician of the study team to give informed consent to the participation in the study.

### Additional consent provisions for collection and use of participant data and biological specimens {26b}

In this study, the patient consents to the performance of all study procedures including the study intervention, blood samples, and further investigations. No storage or biobanking of biological specimens is planned.

### Interventions

#### Explanation for the choice of comparators {6b}

Currently, only few publications investigated the role of CMR to guide TAVR planning. So far, only small trials have been published and they investigate only one aspect (aortic root dimensions or peripheral arteries) of the whole planning procedure [32, 33]. What is more, these studies have not been performed in a randomized fashion.

#### Intervention description {11a}

##### Cardiovascular magnetic resonance (CMR)

All CMR examinations will be performed with a 1.5 T clinical MR imaging unit (AVANTO_fit; Siemens, Erlangen, Germany). The MR protocol consists of a Navigator-gated free breathing 3D “whole-heart” coronary magnetic resonance angiography (MRA), axial 2D true fast imaging with steady-state free precession (true-FISP) during free breathing covering whole body trunk, and a coronal 3D fast low-angle shot (FLASH) Gd-MRA.Navigator-gated free breathing 3D “whole-heart” coronary MRAPlanning of the whole-heart acquisition includes the placement of a cubic field of view at the level of the bulbus aortae as identified at axial, coronal, and parasagittal localizers. The acquisition method is both cardiac triggered and respiratory gated. For an accurate respiratory gating, real-time position of the diaphragm is monitored by the use of navigator echos. A line of signal is reconstructed from each navigator echo and displayed as a trace. The boundary between the low signal intensity in the lung and the relatively high signal intensity in the liver creates an edge that can easily be detected and used as a gating signal, which accurately reflects the diaphragm position and is used to determine whether the data is accepted or rejected. The accuracy of this method allows narrow gating windows (3.5 mm) to be set for high resolution applications. Following MR parameters will be used for this “whole-heart technique”: repetition time (TR) [ms]/echo time (TE) [ms]: 356/1.57; field of view (FOV): 350 × 262 × 58 mm; matrix: 148 × 256 × 72; acquired voxel size: 1.36 × 1.36 × 0.8 mm; flip angle: 90°; and receiver bandwidth: 592 Hz/pixel.3D fast low-angle shot (FLASH) Gd-MRA

Coronal breath-hold fast low-angle shot (FLASH) 3D-MRA will be acquired before and after the intravenous administration of 0.2 mmol/kg of Gd-DO3A-butriol (Gadovist™, Schering, Berlin, Germany) at 2 ml/s, followed by 20 ml of saline flush, administered using an automatic injector (Spectris Injection System, Medrad, Pittsburgh, USA). To define the time delay between contrast injection and image acquisition, we use a semi-automatic synchronization protocol based on the visual inspection of the contrast bolus arrival in the left ventricle (care-bolus). Following MR parameters will be used: TR/TE: 3/1 ms; flip angle: 30°; one excitation; 112 partitions; slice thickness: 1.25 mm; pixel size, 1.3 mm × 1.3 mm × 1.3 mm; acquisition time: 12 s.

##### Computed tomography (CT)

All CT examinations will be performed on a 128-slice dual-source CT (128 mm × 0.6 mm detector collimation, 0.28 s gantry rotation time) and high-pitch factor (3.2; Somatom Definition Flash, Siemens Healthcare, Forchheim, Germany). Prospective electrocardiographic synchronization will be applied, triggered into the diastolic phase for the heart. An injected bolus of 70 to 110 mL of nonionic iodine contrast agent will be applied with 370 mg/mL iodine concentration (Iopromide, Ultravist 370, Bayer Schering Pharma, Berlin, Germany), using an automatic injector at a flow rate of 5 mL/s, followed by 40 mL saline solution. Contrast agent volume for each patient will be calculated by scan time and body weight. Patients will be placed supine with arms overhead. The scan length range from supraaortic branches to the groin.

##### CMR and CT data analysis

Both, an experienced cardiologist and radiologist rate CMR and CT data in a blinded manner. Measurements will be performed at reconstructed 3D “whole-heart” coronary MRA and aortic CTA by rotating the segmented aortic root and left ventricular chamber:
Rating of aortic valve morphology (bicuspid vs tricuspid)Measurements of the aortic annulus at the 3 connection points (“hinge points“) of the aortic valve cusp insertion (“deepest coronary sinus points”)Measurements of coronary ostia heights of the left and right coronary artery (= distance from the annulus)

At true-FISP and contrast-enhanced MRA as well as CTA:
Complete standardized peripheral TAVR-planning including aortic and iliac artery sizing

The choice of prosthesis size for both Edwards Sapien and CoreValve as well as the suitability of the TAVR procedure via femoroiliac access is made for each imaging modality separately, based on manufacturer’s recommendations. Sapien 23 mm is chosen for an annulus perimeter range of 60–70.5 mm, the 26 mm valve for a perimeter range of 70.5–80 mm, and the 29 mm valve for a perimeter range of 80–90 mm, whereas perimeter ranges (69–72 mm) and (78.5–81.5 mm) is considered to fit for both, lower and larger valve size. CoreValve 23 mm is chosen for an annulus perimeter range of 56.5–62.8 mm, the 26 mm valve for a perimeter range of 62.8–72.3 mm, the 29 mm valve for a perimeter range of 72.3–84.8 mm, and CoreValve 31 mm for a perimeter range of 81.7–91.1, whereas perimeter range (81.7–91.1 mm) was considered to fit for both, CoreValve 29 mm and CoreValve 31 mm.

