La Manna et al. investigated 49 patients that were planned to undergo TAVR with TEE and cine steady-state free precession (SSFP) CMR and found a moderate correlation of both methods (*r*^2^: 0.58) regarding aortic annulus size and CMR showed a significant trend to overestimation (TEE 21.4 ± 1.9 mm CMR: 23.7 ± 2.2 mm) [22]. However, annulus sizing was only performed in one dimension in this study. Jabbour et al. investigated 202 consecutive patients, which were scheduled for TAVR with CMR, CT, and TEE and demonstrated a small bias between CMR and CT (0.39 mm) but a large bias between CMR or CT and TEE (4.52 mm and 4.1 mm) for the largest aortic valve (AV) annulus diameter. The authors conclude that CMR and CT are both reliable methods for the sizing of the AV annulus before TAVR [24]. However, in this study, no assessment of peripheral arteries and vascular access routes has been performed. To study the impact of calcification on the agreement of CMR and CT for the sizing of the aortic annulus, Tsang et al. performed ex vivo scans on calcium containing aortic rings and demonstrated that CMR and CT both have a very good correlation with known ring diameters and near zero biases. CMR, however, had smaller limits of agreement than CT (− 0.94 to 1.30 versus − 1.08 to 1.79). Furthermore, an increase in calcification leads to an increase in measurement variability for TEE and CT [25]. Koos et al. compared CMR and CT in 58 patients which were evaluated for TAVR and found no relevant difference between CMR and CT regarding annulus diameter (23.4 ± 1.8 mm and 23.6 ± 1.8 mm, *p* = 0.86), left coronary ostial height (13.2 ± 1.8 mm and 13.3 ± 1.7 mm, *p* = 0.86), and the length of the left coronary leaflet (12.3 ± 1.4 mm and 12.3 ± 1.4 mm, *p* = 0.81). The authors conclude however, “in absence of gold standard a randomized prospective study may give insight into the imaging modality resulting in best procedural outcome” [26]. Recently, Ruile at el. investigated the aortic roots of 69 patients who underwent pre-TAVR CT with 3D non-contrast fast low angle shot (FLASH) CMR and found good agreement of both methods regarding the measurement of aortic annulus area (intraclass correlation 0.961) as well as the distance to the right and left coronary artery (intraclass correlation 0.894 and 0.797) [27]. Promising results have been achieved by Renker et al. in 10 healthy volunteers when comparing a non-contrast self-navigated 3D sequence to a standard 2D-SSFP CMR protocol to study aortic dimensions form the aortic root to the iliac arteries. This study promises a completely contrast-free CMR protocol for the planning of valve size and access routes before TAVR. Although currently the transfemoral approach is predominantly in use, CMR could also be a promising tool enabling to plan TAVR via alternate access routes [28]. However, further feasibility studies in patients with aortic stenosis and calcified peripheral vessels are needed [28]. Novel approaches even utilize real-time CMR for the guidance of TAVR and report easy and effective deployment with the use of the CoreValve and a minimally modified catheter system, which opens the field for a further reduction in contrast and radiation dose during the course of a TAVR procedure [29, 30]. Furthermore, the use of CMR in patients with degenerated bioprosthetic aortic valves before TAVR was shown to be feasible [31].

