#### Primary endpoint

The primary outcome will be a composite clinical efficacy end-point related to implantation success at hospital discharge, based on the VARC-2 criteria [37]Absence of procedural mortalityCorrect positioning of the prosthetic valveIntended performance of the prosthetic valve (mean aortic valve gradient < 20 mmHg and no valve regurgitation > mild)

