## Trial status

The trial protocol has been approved by Ethics Committee of Medical University Innsbruck. The study initiation was held in July 2019. Current study protocol version number 4.0 is basis for this manuscript and written in accordance with the Standard Protocol Items: Recommendations for Interventional Trials (SPIRIT) Statement.

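### The CoreValve 29/31 mm dual-fit zone (81.7–91.1 mm) repeats the whole 31 mm range and runs 6.3 mm past the 29 mm limit; the two stated ranges overlap only at 81.7–84.8 mm

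*Protocol article*

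**What the plan says.** The section CMR and CT data analysis of the protocol article sets perimeter ranges for choosing prosthesis size. The choice is made separately for each imaging modality and is said to follow the manufacturer's recommendations.

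- For the two largest CoreValve sizes it gives: "the 29 mm valve for a perimeter range of 72.3–84.8 mm, and CoreValve 31 mm for a perimeter range of 81.7–91.1".
- It then defines the zone in which either size is acceptable: "whereas perimeter range (81.7–91.1 mm) was considered to fit for both, CoreValve 29 mm and CoreValve 31 mm".
- The Sapien rule in the same paragraph has dual-fit zones as well: "whereas perimeter ranges (69–72 mm) and (78.5–81.5 mm) is considered to fit for both, lower and larger valve size". These sit around ranges that meet at 70.5 mm and 80 mm.

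No other section restates or corrects the CoreValve figures.

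**The concern.** The dual-fit zone has the same two endpoints as the 31 mm range. For perimeters of 84.8–91.1 mm the paragraph therefore puts the 29 mm valve out of range in one clause and calls it suitable in the next.

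This is a decision threshold in a rule for choosing valve size from each imaging modality, and planning from each modality is what the trial compares. Taken literally, it allows a 29 mm valve in annuli well above that valve's stated limit. Valve size plausibly bears on two parts of the primary endpoint: correct positioning, and the requirement of "no valve regurgitation > mild".

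**Working it through.** **Inputs** (protocol article, CMR and CT data analysis, perimeters in mm)

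- CoreValve 29 mm: 72.3–84.8
- CoreValve 31 mm: 81.7–91.1
- Stated zone fitting both: 81.7–91.1
- Sapien 23, 26 and 29 mm: 60–70.5, 70.5–80 and 80–90; dual-fit zones 69–72 and 78.5–81.5

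**1. Try to reproduce the stated zone.** The overlap of two ranges runs from the larger lower limit to the smaller upper limit.

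- Lower end: max(72.3, 81.7) = 81.7
- Upper end: min(84.8, 91.1) = 84.8
- Overlap: 81.7–84.8, width 84.8 − 81.7 = 3.1 mm

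The stated zone is 91.1 − 81.7 = 9.4 mm wide, so it is not reproduced. Its lower end agrees; its upper end is the 31 mm valve's upper limit.

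**2. Size of the overrun.** The zone passes the 29 mm limit by 91.1 − 84.8 = 6.3 mm. That is 6.3/9.4 = 67% of the zone.

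**3. Compare with Sapien.**

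| | Sapien 23/26 | Sapien 26/29 | CoreValve 29/31 |
|---|---|---|---|
| Nominal ranges | meet at 70.5 | meet at 80 | overlap by 3.1 mm |
| Dual-fit width | 72 − 69 = 3.0 mm | 81.5 − 78.5 = 3.0 mm | 9.4 mm |
| Overrun past smaller valve's limit | 72 − 70.5 = 1.5 mm | 81.5 − 80 = 1.5 mm | 6.3 mm |
| Share of larger valve's range covered by this zone | 1.5/9.5 = 15.8% | 1.5/10 = 15.0% | 9.4/9.4 = 100% |

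The CoreValve overrun is 6.3/1.5 = 4.2 times the Sapien overrun. The 3.1 mm overlap already present in the CoreValve ranges is about as wide as a Sapien band.

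**4. How many patients could fall in 84.8–91.1 mm.** Assuming circular annuli, diameter = perimeter/π: 84.8/π = 26.99 mm and 91.1/π = 29.00 mm. The Background and rationale section reports diameters from two cohorts: "annulus diameter (23.4 ± 1.8 mm and 23.6 ± 1.8 mm" for CMR and CT, and "TEE 21.4 ± 1.9 mm CMR: 23.7 ± 2.2 mm" in a comparison of TEE with CMR. Assuming normal distributions:

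| Diameter distribution | P(26.99 < D < 29.00) | × 250 patients |
|---|---|---|
| 23.4 ± 1.8 (CMR) | 2.20% | 5.5 |
| 23.6 ± 1.8 (CT) | 2.84% | 7.1 |
| 23.7 ± 2.2 (CMR, one-dimensional sizing) | 5.92% | 14.8 |

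Only CoreValve recipients count. Their share is not stated; I assume 25–75%.

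- Full range: 5.5 × 0.25 = 1.4 to 14.8 × 0.75 = 11.1 patients
- CMR/CT cohort only: 1.4 to 7.1 × 0.75 = 5.3 patients

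**The case against.** The best defence is that a dual-fit clause is an exception, and exceptions are meant to override nominal limits. The Sapien zones do so, so passing a limit proves nothing by itself. That is fair. What remains is the form of the CoreValve zone. Sapien ranges abut, so a grey zone has to be added, and both added bands are symmetric. The CoreValve 29 and 31 mm ranges already overlap. The stated zone extends that overlap on one side only, up to the top of the 31 mm range. No perimeter is then left for the 31 mm valve alone, and the 84.8 mm limit has no function.

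Four further objections stand in part.

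- **Intended value.** That 84.8 was meant and 91.1 was copied from the preceding range is an inference. The manufacturer's chart is not in the documents.
- **Force of the rule.** The paragraph ties the choice to the manufacturer's recommendations, and the section on concomitant care leaves clinical care unrestricted. Whether the printed figures governed implantation cannot be settled from the article. The reference to the manufacturer limits the harm but does not resolve two figures that disagree.
- **Patient count.** It is a ceiling on exposure, not a count of wrongly sized valves. Its upper end rests on a cohort sized in one dimension, which converts poorly to a perimeter. The 31 mm valve also fits the whole zone, so a patient is affected only if someone picks the 29 mm valve.
- **Consequence for the comparison.** The thresholds are the same in both arms, and neither the margin nor the sample size uses them.

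**Conclusion.** The inconsistency is real and follows from the article's own figures, without any outside source. Confidence in it is high. Confidence in 81.7–84.8 mm as the intended zone is lower, since that is inferred from the two ranges and the Sapien pattern.

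The severity is minor. The likely exposure is a handful of patients, on the stated assumptions of circular annuli, normally distributed diameters and a 25–75% CoreValve share. The link to positioning and regurgitation is plausible but not quantified. I claim no directional bias between the arms.

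**What to change.** Change the CoreValve 29/31 mm dual-fit zone to 81.7–84.8 mm, so that 84.8–91.1 mm is for the 31 mm valve only. First confirm this against the manufacturer's recommendation and the full protocol, since the article states: "Current study protocol version number 4.0 is basis for this manuscript".

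If version 4.0 has the right figure, a one-figure correction to the article is enough. If it carries the same error, correct it there too and re-check the size chosen for CoreValve patients with a perimeter above 84.8 mm. The cost is one edited number and, at most, a review of a few reads.
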